### Randomization

44 participants each will receive a different treatment as allocated to Groups 1 and 2 after scaling and root planing are completed. For the participant referring to Group I, oxygen-releasing gel will be administered locally, and for Group II, the supra and subgingival areas will be treated with SRP therapy alone. The flip coin approach will be used for randomization in order to distribute participants into Groups I and II. A separate researcher who is not involved in the methods will create the allocation sequence.

### Procedure

Participants will be enrolled and randomly assigned to interventions by the researchers in charge of the therapy application. Researchers will undergo training before data collection and evaluations, following the procedures and outcome measures outlined. The UNC-15 probe, which measures plaque index (PI), FMBS, Probing Pocket Depth (PPD), and CAL, will be used to evaluate participants’ periodontal clinical characteristics. Every patient will get instructions on the proper brushing technique as well as a demonstration of good oral hygiene practices.

At the first appointment, each patient will receive full-mouth supragingival scaling. After 1 week, on the second appointment, under local anesthesia of 2% lidocaine with 1:100,000 epinephrine, subgingival root planing will be done using Gracey curettes (Hu-Friedy). Following subgingival SRP, the experimental site will be segregated for patients in Group I. Oxygen-releasing gel will be administered in all sites with a probing depth of ≥4 mm over the course of five to ten minutes [7].

Regarding patients in Group II, they will be treated with subgingival SRP alone.

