**Methods:**

Twenty-two systemically healthy people with sites of chronic periodontitis were the participants of a split-mouth randomized controlled experiment. For every patient, two locations were chosen and divided into two groups at random. In total, 44 sites were chosen and divided into two groups: Group I (the test group) consisted of 22 test sites, while Group II (the control group) consisted of 22 control sites. While group II underwent SRP alone, group I underwent SRP followed by the use of BlueM oral gel. Plaque index, full mouth bleeding score, clinical attachment level, and probing pocket depth were measured at baseline, one month, and three months, and were compared appropriately.

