### Sample size estimations

The sample size was calculated using the formula for comparison of two independent means:

$$\begin{array}{l} n1=(\sigma 12+\sigma 22/\kappa )(Z1-\alpha /2+Z1-\beta )2\Delta 2n_{1}\\ =\frac{(\sigma_{1}^{2}+\sigma_{2}^{2}/\kappa )(Z_{1-\alpha /2}+Z_{1-\beta }{)}^{2}}{\Delta^{2}}n1\\ =\Delta 2(\sigma 12+\sigma 22/\kappa )(Z1-\alpha /2+Z1-\beta )2 \end{array}$$

where n₁ and n₂ represent the sample sizes of groups 1 and 2, respectively; σ₁ and σ₂ denote the standard deviations of groups 1 and 2; Δ represents the expected difference in group means; κ is the allocation ratio (n₂/n₁); Z₁-α/2 corresponds to the standard normal deviate for a two-sided significance level (1.96 for a 95% confidence interval); and Z₁-β represents the standard normal deviate corresponding to the study power (0.84 for 80% power).

Based on previous findings reported by Anuradha et al [14], the mean Gingival Index was 0.52 in group I and 0.88 in group II, with standard deviations of 0.51 and 0.33, respectively. The expected mean difference (Δ) was therefore calculated as 0.36 (0.88 − 0.52). Assuming an allocation ratio (κ) of 1, a power of 80%, and a significance level of 5% (two-sided), the calculated sample size was 22 participants per group.

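### Randomization and Procedure allocate and treat whole patients, which contradicts the split-mouth design of 22 patients with one gel site and one SRP-alone site each

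*Protocol article*

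**What the plan says.** Two descriptions of the trial stand in the current text of the protocol article.

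**Split-mouth, 22 patients.** The Methods part of the Abstract calls the trial split-mouth and makes the site the unit of allocation: "For every patient, two locations were chosen and divided into two groups at random". It counts 44 sites: "Group I (the test group) consisted of 22 test sites, while Group II (the control group) consisted of 22 control sites". Strengths of This Study says that each patient receives both treatments, on separate sides of the mouth, and serves as their own control. Limitations again calls the design split-mouth.

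**Parallel groups, 44 patients.** Randomization begins: "44 participants each will receive a different treatment as allocated to Groups 1 and 2". It then gives the method: "The flip coin approach will be used for randomization in order to distribute participants into Groups I and II". Procedure divides the treatment by patient. For the gel group, "the experimental site will be segregated for patients in Group I", followed by "Oxygen-releasing gel will be administered in all sites with a probing depth of ≥4 mm over the course of five to ten minutes". For the other group: "Regarding patients in Group II, they will be treated with subgingival SRP alone". Sample size estimations uses the formula for two independent means and concludes that "the calculated sample size was 22 participants per group".

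Statistical Analysis lists both paired and unpaired t tests. Results reports 22 participants enrolled as of January 2026, with recruitment ongoing.

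**The concern.** The unit of randomisation determines how each patient is treated, how many patients are needed and which analysis is valid. Here it is stated twice, in incompatible ways.

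The sections that tell staff what to do are Randomization and Procedure. Staff who followed them as written would put each patient wholly into one group. No patient would then contribute both a gel site and an SRP-alone site, and the own-control comparison that the article claims as a strength would not exist. The recruitment target is also unclear: on one reading enrolment is complete, on the other it is half done.

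**Working it through.** **1. The two versions side by side**

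| Item | Abstract, Strengths | Sample size estimations, Randomization, Procedure |
|---|---|---|
| Unit allocated | site, two per patient | participant |
| Number of patients | 22 | 44 (22 per group) |
| Gel placed in | one site per patient | all pockets of 4 mm or deeper in Group I patients, read literally |
| SRP alone | the other site of the same patient | patients in Group II |
| 22 enrolled, share of target | 22/22 = 100% | 22/44 = 50% |

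Reading 44 participants as a slip for 44 sites (2 × 22) does not remove the conflict. The coin toss is still said to distribute participants, Procedure still assigns patients to groups, and the sample size is still given in participants per group.

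**2. The article's own sample size**

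Inputs from Sample size estimations: SDs 0.51 and 0.33, difference 0.36, two-sided 5%, 80% power, ratio 1.

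n per group = (0.51² + 0.33²)(1.96 + 0.84)² / 0.36² = 0.3690 × 7.84 / 0.1296 = 22.32

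The stated 22 is reproduced (23 if rounded up). The formula is for independent groups, so 22 per group means 44 patients. That agrees with Randomization and not with the Abstract.

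**3. What the coin toss yields**

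- Tossed over 44 participants: P(exactly 22 v 22) = C(44,22)/2⁴⁴ = 0.1196, or 12.0%.
- Tossed within each of 22 patients: always 22 gel sites and 22 SRP-alone sites.

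Only the second guarantees the 22 + 22 sites that the Abstract reports.

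**4. Power, for scale only**

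The only inputs given are for the Gingival Index, which is not the primary outcome. None are given for probing depth. The within-patient correlation ρ is not in the document and is assumed. Power is from the noncentral t distribution, two-sided 5%.

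- Parallel, n per group: pooled SD = √(0.3690/2) = 0.4295; noncentrality = 0.36 / (0.4295 × √(2/n)); df = 2n − 2.
- Paired, 22 patients: SD of the difference = √(0.3690 − 2ρ × 0.51 × 0.33); noncentrality = 0.36 × √22 / SD; df = 21.

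| Design | SD used | Power |
|---|---|---|
| Parallel, 22 v 22 | 0.4295 | 77.5% |
| Paired, 22 patients, ρ = 0 | 0.607 | 75.5% |
| Paired, 22 patients, ρ = 0.3 | 0.518 | 87.5% |
| Paired, 22 patients, ρ = 0.5 | 0.448 | 94.9% |
| Parallel, 11 v 11 | 0.4295 | 46.5% |

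Against 22 v 22 in parallel, 22 pairs range from 2 points lower (75.5 − 77.5) to 17 points higher (94.9 − 77.5). The two are equal at ρ of about 0.05. The last row applies only if recruitment stopped at 22 and those patients had been treated in parallel groups.

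**The case against.** The strongest reply is that the trial is plainly split-mouth and the rest is loose drafting. Three sections name that design, eligibility asks for at least two or three deep sites per patient, and 44 is exactly twice 22. The gel rule can be read to fit: it may mean all Group I study sites across patients, or all deep sites on the gel side of each mouth. Procedure also mentions setting the experimental site apart. The article condenses a fuller protocol that staff may be using, and nothing shows that any patient was treated wholly in one group. Listing both t tests is common, since paired tests can serve change over time. The power figures use a different outcome and an assumed correlation.

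Much of this stands. The gel sentence alone is ambiguous, and Randomization is the firmer evidence. Gel in a control site is an unlikely reading, given the neighbouring sentences. How patients have actually been treated is unknown. The list of t tests proves nothing either way, and the power figures do not measure harm.

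It does not remove the contradiction. Under either kinder reading of the gel rule, the coin still distributes participants and Procedure still treats Group I and Group II as different patients. Nor is this detail left to another document: the article states the unit of allocation, and states it inconsistently.

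Two related matters are separate points and leave this one standing: the independent-means formula under a paired design, and the full-mouth bleeding score, which gives one value per mouth.

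**Conclusion.** The concern holds. The article describes two trials that cannot both be carried out: 22 patients with paired sites, or 44 patients in two groups. The conclusion rests on the text and needs no assumption about outcomes or correlation. Its firm size is the factor of two in the number of patients, which leaves enrolment at either 100% or 50% of target, together with the loss of the within-mouth comparison if Randomization and Procedure are followed literally. The effect on power is indicative only, because it borrows Gingival Index inputs and assumes ρ between 0 and 0.5. The point should be fixed now, while data collection continues and the analysis is not complete.

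**What to change.** 1. **Check the records first.** For every patient already treated, establish which sites received gel and which received SRP alone. Report any SRP-alone site exposed to gel and any patient treated wholly in one group. Rewording before this check could misdescribe what was done.
2. **Randomization.** State that within each of the 22 patients the coin assigns one of the two selected sites to gel and the other to SRP alone. Replace the 44 participants with 22 patients and 44 sites.
3. **Procedure.** Describe treatment by site, and state that gel is never placed in the SRP-alone site. Drop the instruction to treat all deep sites, or limit it so that the control site is clearly excluded.
4. **Sample size estimations.** Give the number as 22 patients, each contributing one site per group.
5. **Primary comparison.** Define it as the two allocated sites within each patient, analysed as randomised and paired.

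The cost is wording in three sections and a line on the primary comparison, one field on the treatment form for the site that received gel, and a review of the records of patients already treated.

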### Statistical Analysis

The calculation of mean and SD will be done, and the mean data will be analyzed using a standard statistical method to determine statistical significance. Examiners performing outcome assessments are blinded to group allocation. The study includes assessor blinding. Outcome assessors will be unaware of participant group allocation to reduce potential bias. All assessments will be conducted using standardized tools to maintain consistency and objectivity. Data from the baseline, one month, and three months for each group will be evaluated using descriptive and inferential statistics, including the *χ*^2^ test, Student paired and unpaired t test, one-way ANOVA, and Tukey test. The analysis will be conducted using SPSS (version 27.0; IBM Corp) and GraphPad Prism (version 7.0) software, with a significance threshold of *P*<.05. A *P* value below 0.05 will be regarded as significant, but a *P* value above 0.05 will be regarded as not statistically significant.

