### Evaluation Outcomes

The primary outcome of this study is to measure probing pocket depth, and secondary outcomes will be PI, FMBS, and CAL.

Secondary outcomes would complement the primary clinical measurements, providing a more comprehensive understanding of how the oxygen-releasing gel contributes to the overall treatment of chronic periodontitis when added to SRP.

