### Strengths of This Study

A randomized controlled trial design, which is regarded as the gold standard for clinical research, is used in this investigation. Dividing individuals into the experimental and control groups at random lowers biases and improves the reproducibility of the findings. Each participant can function as their control thanks to the split-mouth design. As each patient receives both the normal treatment (SRP) and the experimental treatment (oxygen-releasing gel) on separate sides of their mouth, this reduces interpatient variability. Measurable clinical outcomes that are objective indicators of periodontal health and treatment efficacy, like the PI, FMBS, PPD, and CAL, are probably used in this study. This makes it possible to evaluate the oxygen-releasing gel’s effectiveness with clarity.

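### The listed tests include three that assume independent observations, and nothing ties the paired t test to the test-versus-control comparison that a split-mouth trial needs.

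*Protocol article*

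**What the plan says.** The Abstract (Methods) describes a split-mouth randomised trial in 22 people: "For every patient, two locations were chosen and divided into two groups at random", and "In total, 44 sites were chosen and divided into two groups", 22 test and 22 control. Strengths of This Study gives the reason for the design: "Each participant can function as their control thanks to the split-mouth design".

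Evaluation Outcomes sets the endpoint: "The primary outcome of this study is to measure probing pocket depth". The first item under Objectives compares the reduction in probing depth with and without the gel.

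Statistical Analysis states: "Data from the baseline, one month, and three months for each group will be evaluated using descriptive and inferential statistics". The methods it then names are the chi-square test and "Student paired and unpaired t test, one-way ANOVA, and Tukey test". No test is attached to a comparison, and no method for correlated sites or repeated visits is named apart from the paired t test.

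Other sections read as a parallel-group trial. Randomization says "44 participants each will receive a different treatment as allocated to Groups 1 and 2", Procedure refers to patients in Group I and patients in Group II, and Sample size estimations uses the formula for two independent means and arrives at 22 participants per group.

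**The concern.** In a split-mouth trial, the test and control sites belong to the same patient, and the baseline, 1-month and 3-month readings come from the same sites. The unpaired t test, one-way ANOVA and Tukey test treat such readings as independent. With only two groups, the natural use of one-way ANOVA followed by Tukey is across the three visits, where independence fails.

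The paired t test would suit the gel-versus-control contrast, but the text does not assign it there. A common reading of such a list is paired t for change within a group and unpaired t between groups. On that reading the primary comparison would discard the within-patient pairing that the protocol presents as a strength. Its standard error would be too large whenever the two sites are positively correlated. Leaving both tests open also leaves room to choose between them once the data are known.

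**Working it through.** **Inputs from Sample size estimations (Gingival Index; the article gives no probing-depth figures).** Means 0.52 and 0.88, difference 0.36; SDs 0.51 and 0.33; 80% power; two-sided 5%; allocation ratio 1.

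**Reproducing the stated sample size.** n = (0.51² + 0.33²)(1.96 + 0.84)² / 0.36² = (0.3690 × 7.84) / 0.1296 = 22.32. The stated 22 is this value rounded down; rounding up gives 23. The calculation treats the groups as independent.

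**Assumption.** The within-patient correlation ρ is not in the document, so a range is used.

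**Test versus control, 22 patients with one site of each kind.** The variance of the within-patient difference is 0.51² + 0.33² − 2ρ(0.51)(0.33) = 0.3690 − 0.3366ρ. The standard error that ignores pairing exceeds the correct one by the factor √[0.3690 / (0.3690 − 0.3366ρ)]. Type I error (nominal 5%) and power at a difference of 0.36 come from simulation.

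| ρ (assumed) | SE ratio, unpaired / paired | Type I error, unpaired | Power, unpaired | Power, paired |
|---|---|---|---|---|
| 0 | 1.00 | 5.1% | 78% | 76% |
| 0.2 | 1.11 | 3.2% | 80% | 83% |
| 0.3 | 1.17 | 2.4% | 81% | 88% |
| 0.5 | 1.36 | 1.0% | 84% | 95% |
| 0.7 | 1.66 | 0.2% | 88% | 99% |

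The paired test holds about 5% throughout. At ρ = 0 it is marginally less powerful, because it has 21 rather than 42 degrees of freedom.

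**Three visits within one group, 22 patients, equal correlation between visits.** The actual size of one-way ANOVA at nominal 5% is about 4.9% at ρ = 0, 1.6% at 0.3, 0.4% at 0.5 and under 0.1% at 0.7. Repeated-measures ANOVA stays near 5%. For an illustrative linear change of 0.6 SD from baseline to 3 months, power at ρ = 0.3, 0.5 and 0.7 is 35%, 31% and 25% for one-way ANOVA, against 52%, 68% and 89% for repeated measures.

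**Direction.** With one reading per site in the comparison, these errors are conservative. If all three visits were pooled as separate observations in an unpaired t test, the error could reverse: 16.6% type I error with a visit correlation of 0.5 and no correlation between sites. The plan does not say that it will pool visits.

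**The case against.** The strongest reply is that the paired t test is already on the list. No test is assigned to a contrast, and an article may leave that to a fuller plan, so a reader who infers that the trial will analyse its primary outcome with the wrong test goes beyond the text. This stands: the plan permits the wrong analysis but does not commit to it. It could also be said that one-way means one factor and need not exclude a repeated-measures form. That is possible, but nothing in the section says so.

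Second, Sample size estimations, Randomization and Procedure read as two groups of different people. If that were the design, an unpaired t test between groups would be valid, although ANOVA across visits would still have to respect repeated measurement. The Results section's 22 enrolled with recruitment ongoing does not settle which design is meant. This also stands, and it makes the fix conditional.

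Three stronger readings are tempting but not supported:

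- **A collapse in power.** Unpaired power of 54% or 26% (ρ = 0.5 or 0.7) appears only if the true difference is shrunk as correlation rises, so that the paired test always has 80%. That means differences of 0.63 and 0.49 SD. The protocol's own inputs give 0.36 / √(0.3690 / 2) = 0.36 / 0.43 = 0.84 SD, at which unpaired power stays near or above the planned 80%.
- **A false claim of benefit from within-group tests.** If both sites truly improved equally, a significant change in the test group alone could occur in 13–24% of trials under assumed effects. That matters only if efficacy is inferred from this pattern. The plan states no such rule, and its Objectives are comparisons between treatments.
- **Baseline depth goes unused.** The objective is reduction in depth, which already uses baseline. Further covariate adjustment is an option whose absence is not an error.

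**Conclusion.** The point holds in a limited form. If the trial is split-mouth, three of the listed tests do not fit its data, and the one that does is not attached to the primary contrast. Choosing the unpaired test would cost about 7 to 11 percentage points of power at the planned difference for ρ between 0.3 and 0.7, and its standard error would be 1.17 to 1.66 times the correct one. Using one-way ANOVA across visits would give a test with actual size of about 1.6% or less over the same range.

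These sizes rest on an assumed correlation, on Gingival Index inputs standing in for probing depth and, for ANOVA, on equal correlation between visits. Near zero correlation the loss is negligible. The likely harm is a missed effect or an over-wide interval, not a spurious benefit. ANOVA within a group does not itself test the gel against control, so it bears on the visit comparisons and not on the primary objective.

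**What to change.** 1. Reconcile the design first. Sample size estimations, Randomization and Procedure (two groups of participants, 44 in all) must agree with the Abstract and Strengths of This Study (22 patients with paired sites).
2. If split-mouth is confirmed, state one primary analysis: the within-patient test-minus-control difference in probing-depth reduction, with a 95% confidence interval. Use a paired t test or a mixed model with a patient effect; baseline depth is an optional covariate.
3. Drop the unpaired t test for this contrast.
4. Replace one-way ANOVA and Tukey across visits with a repeated-measures or mixed-model method.
5. State that changes within each group are descriptive and are not evidence of a gel effect.

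The cost is revised wording and slightly more analysis work. No new data are needed, and the SPSS version already named can fit a mixed model. The Results section says the analysis is not yet complete, so the change can be made and dated before it is.

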### Evaluation Outcomes

The primary outcome of this study is to measure probing pocket depth, and secondary outcomes will be PI, FMBS, and CAL.

Secondary outcomes would complement the primary clinical measurements, providing a more comprehensive understanding of how the oxygen-releasing gel contributes to the overall treatment of chronic periodontitis when added to SRP.

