
### Objectives

To compare the reduction in probing depth following scaling and root planing (SRP) with and without the application of oxygen-releasing gel in the treatment of chronic periodontitisTo evaluate the gain in clinical attachment level after SRP with and without the adjunctive use of oxygen-releasing gelTo assess the reduction in Full Mouth Bleeding Score (FMBS) as an indicator of improved periodontal health following SRP with and without the oxygen-releasing gel

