#### Inclusion Criteria

Participants eligible for the study were motivated to undergo therapy and complete follow-up visits. Individuals who provided written informed consent were included. Participants were required to have a minimum of 15 natural teeth and be in good physical and systemic health. Only patients with clinical attachment loss ≥1 mm and diagnosed with chronic generalized periodontitis, presenting with at least 2–3 sites exhibiting periodontal pocket depths ≥4 mm, were selected for the study.

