## Results

The study was not funded. Recruitment began in April 2025 and is ongoing. As of January 2026, 22 participants have been enrolled. Data collection is ongoing, and statistical analysis has not yet been completed. The results are expected to be published in Winter 2026. All the clinical measurements will be recorded at the baseline, 1 month, and 3 months. PIFMBS, PPD, and CAL will be used to assess the patient’s dental hygiene state. Oxygen-releasing gel may exhibit a higher reduction in clinical parameters.

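### The primary outcome is named as pocket depth without saying final value or change, and the listed tests leave the collected baseline depth unused; a pair-respecting baseline adjustment settles both at small cost.

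*Protocol article*

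**What the plan says.** In the Protocol article, Evaluation Outcomes gives the primary outcome in one sentence: "The primary outcome of this study is to measure probing pocket depth, and secondary outcomes will be PI, FMBS, and CAL". It attaches neither a metric (final value or change) nor a visit. The first item under Objectives is worded as a change: "To compare the reduction in probing depth following scaling and root planing (SRP) with and without the application of oxygen-releasing gel".

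On timing, Results says: "All the clinical measurements will be recorded at the baseline, 1 month, and 3 months". No visit is singled out as primary.

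On the sites, the Abstract describes two locations per patient, allocated at random, giving 22 test and 22 control sites. Inclusion Criteria sets a floor on depth for patients, "presenting with at least 2–3 sites exhibiting periodontal pocket depths ≥4 mm". The article states no upper limit and no matching of the two sites on depth.

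On analysis, Statistical Analysis says: "Data from the baseline, one month, and three months for each group will be evaluated using descriptive and inferential statistics". The methods it then lists are the chi-square test, paired and unpaired t tests, one-way ANOVA and the Tukey test. None of these, as listed, takes baseline depth as a covariate.

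**The concern.** Final depth and reduction are different variables when the two sites of a pair do not start at the same depth. If the test sites happen to start deeper, their final depths tend to be deeper too, which counts against the gel. Their reductions tend to be larger, because part of any high starting value does not persist, and this counts in its favour. With only 22 pairs some imbalance is expected.

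Two things are at stake. The first is precision: an unadjusted analysis carries baseline noise that could be removed with data already in hand. The second is that the outcome sentence leaves the choice of metric open. If that choice were made after the results were seen, the conclusion could depend on it.

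**Working it through.** **The plan's own figure.** Sample size estimations uses SDs 0.51 and 0.33, difference 0.36, and deviates 1.96 and 0.84:

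(0.51² + 0.33²) × (1.96 + 0.84)² / 0.36² = 0.369 × 7.84 / 0.1296 = 22.32.

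The stated 22 per group reproduces, rounded down. The inputs are for the Gingival Index, so they give neither an SD nor a correlation for pocket depth. Both must be assumed below.

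**Inputs.** n = 22 pairs (Abstract). Let B and F be the test-minus-control differences in depth at baseline and at follow-up within a patient. Assumptions: normal data, equal SD of B and F, and correlation r between them, varied over a range.

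**Size of chance imbalance.** If B has SD 1 mm, the mean of B has standard error 1/√22 = 0.213 mm. Put another way, with a site-level SD of 1 mm and within-patient correlation c, the standard error is √(2(1 − c)/22). That is 0.30, 0.21 and 0.17 mm at c = 0, 0.5 and 0.7.

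**Direction.** Given a mean baseline imbalance d, the expected shift is r × d in final depth and −(1 − r) × d in change (follow-up minus baseline). At r = 0.5, an imbalance of 1 to 2 standard errors moves final depth by 0.11 to 0.21 mm one way and change by the same amount the other way.

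**Precision.** Variance of the estimate relative to final depth:
- change: 2(1 − r)
- adjusted (F regressed on B, effect = intercept): (1 − r²) × (n − 2)/(n − 3) = (1 − r²) × 20/19

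Power is from 200,000 simulated trials per value of r, with the effect set so that a paired t test on final depth has 80%.

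| r | Variance: final / change / adjusted | Power: final / change / adjusted |
|---|---|---|
| 0 | 1.00 / 2.00 / 1.05 | 80 / 51 / 78% |
| 0.3 | 1.00 / 1.40 / 0.96 | 80 / 66 / 82% |
| 0.5 | 1.00 / 1.00 / 0.79 | 80 / 80 / 88% |
| 0.7 | 1.00 / 0.60 / 0.54 | 80 / 95 / 97% |
| 0.9 | 1.00 / 0.20 / 0.20 | 80 / 100 / 100% |

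**Break-even.** Against final depth: (1 − r²) × 20/19 = 1 gives r² = 0.05, so |r| ≈ 0.22. Against change: (1 + r) × 20/19 = 2 gives r = 0.90. Outside that range the loss is at most a factor of 20/19, about 5%.

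**Validity.** Simulated type I error is about 5% for all three analyses. Among null trials whose baseline imbalance exceeds 1 standard error, at r = 0.5, it is about 9% for either unadjusted version and 5% for the adjusted one. If the metric were chosen after the results were seen, the chance that at least one unadjusted version is significant under the null is about 9% for r from 0.3 to 0.7.

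**Same estimate either way.** If F = a + bB + error, then F − B = a + (b − 1)B + error. The intercept a is unchanged. For reduction, written as baseline minus follow-up, only its sign flips.

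**The case against.** The strongest reply is that there is no real contradiction. Evaluation Outcomes names a variable and Objectives states the comparison made on it, so the two together read naturally as pocket depth analysed as reduction. That largely stands. A reader might infer two rival primary endpoints, but nowhere does the article declare raw follow-up depth to be the endpoint. What remains is loose wording on metric and visit.

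Second, covariate adjustment is commonly left to an analysis plan, and the test list is introduced as an inclusion, so it need not be exhaustive. That also stands: the absence of an adjusted model from an article is not an error in itself. The point is that the methods actually named leave collected information unused, and a better one is available.

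Third, a reader might infer that baseline imbalance biases the trial. It does not. Under random allocation it averages to zero, and the unadjusted tests keep their 5% level. What remains is noise, and error conditional on the imbalance that occurred.

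Fourth, a reader might cite the Abstract's remark that scaling and root planing has trouble reaching deeper pockets as evidence that reduction favours the deeper arm. That remark, if anything, suggests a poorer response in deep sites. The opposite-direction result above rests on the correlation assumption, not on that remark.

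Finally, adjustment is not free and not always the most precise choice, as the break-even values show.

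**Conclusion.** The point holds as one of wording and efficiency, not validity. The primary outcome lacks a metric and a visit, and the listed tests do not use baseline depth. The chance imbalance has a standard error of about 0.21 mm if the pair difference has an SD of 1 mm, which is an assumption. Adjustment gains when r lies between about 0.22 and 0.90. At r = 0.5 it cuts the variance by about 21% against either unadjusted version (0.79 against 1.00). The gain is likely but cannot be guaranteed, because the article gives no SD or correlation for pocket depth.

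Adjustment removes the depth-versus-reduction ambiguity. It does not choose between 1 and 3 months, so that part of the endpoint must be settled separately. The paired model also presupposes one test and one control site per patient. The article is not consistent on this: the Abstract and Strengths of This Study describe a split-mouth design, while Randomization speaks of 44 participants allocated to two groups, and Procedure has gel applied in every site of 4 mm or more for Group I patients.

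**What to change.** Before analysis, amend Evaluation Outcomes and Statistical Analysis to say:

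- The primary analysis is the within-patient test-minus-control difference in probing pocket depth at one named follow-up visit (1 or 3 months, to be chosen by the investigators), regressed on the within-patient difference in baseline probing pocket depth. The treatment effect is the intercept, with its 95% confidence interval.
- The same model is used for CAL.

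Reconcile Randomization and Procedure with the split-mouth description in the Abstract and Strengths of This Study, so that it is clear the paired model applies. Results says the statistical analysis is not yet completed, so record the date of the amendment and confirm that outcomes by arm had not been examined.

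The cost is a few sentences and one regression on data already collected. It uses one of 21 residual degrees of freedom and at most about 5% in variance (at r = 0, power falls from 80% to 78%). No extra patients or visits are needed. No change to site selection is proposed, since Results reports 22 participants already enrolled, the number given in the Abstract.
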